### Interventions

#### Healing hearts together intervention

Couples are invited to attend 8 weekly 2-h sessions facilitated by clinical psychologists with EFT training. Before providing the intervention, facilitators review information on CVD and its treatments, theory and practice of group interventions, and familiarize themselves with the HHT facilitator materials. An HHT facilitators manual was developed to standardize intervention delivery (Tulloch et al., 2017). Planned group size is 3–8 couples, with sessions available in the day or evening to accommodate participants’ work schedules. Since the onset of the COVID-19 pandemic (March 2020), however, groups have been conducted online using the secure platform Zoom; only one group was held in-person before the pandemic. During the program, participants are guided through seven conversations in which they learn to identify and improve communication patterns for positive interactions in relationships (Tulloch et al., 2021). EFT interventions allow couples to acknowledge their fears and vulnerabilities and solidify their sense of security and emotional connection by guiding partners to respond to these feelings in comforting ways (Johnson, 2004; Johnson, 2008). The intervention maintains principles from the *Hold Me Tight* program (Johnson, 2010) but, as alluded to above, centres on identifying the impact of CVD on relationship dynamics, including the recognition and processing of worries and emotions following a cardiac diagnosis or event, healing interactions, and discussing sexuality in a health context (Tulloch et al., 2021). Materials, such as in-class and take-home worksheets, didactic presentations, and videos, are incorporated to facilitate these conversations (Johnson, 2010; Tulloch et al., 2021). The session-by-session overview has been previously described (Tulloch et al., 2021). In brief, each session begins with a review of the previous session and its homework, followed by a didactic presentation, a video clip of a couple discussing EFT principles, a private dyadic conversation, a final group discussion, and a homework assignment. In addition, each couple receives a copy of the book, *Hold Me Tight*, in print or audio version (Johnson, 2008) to be read in-between sessions. Attendance is noted at each session. Participants are asked to inform research staff if they must miss a session, and if this is the case, they are sent presentation slides from the respective session for review. Participant feedback surveys are sent via email after each session. All sessions incorporate group discussions and private conversations between patients and partners. Group discussion allows couples to share experiences related to CVD with their partners and peers. Session two allows for participants to discuss their experiences as patients in a patient-only group and as partners of someone with CVD in a partner-only group discussion, both of which are guided by a facilitator. Zoom break-out rooms are used for dyadic-specific exercises; facilitators assist during these discussions. HHT intervention materials may be found here: https://iceeft.com/healing-hearts-together-relationship-education-program/.

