### Statistical analyses

#### Sample-size calculation

An *a priori* calculation was performed using RQ as measured by the DAS at 8 weeks as the primary outcome. Sample size was derived in 3 steps. First, we examined the standard deviation (SD) of the DAS scores pre-post intervention (SDchange) of pilot patients and partners separately (i.e., HHT pilot data); all SDchange values were close to 10. The consensus of the study investigators and other clinical content experts was to identify a minimum clinically important difference (MCID) based on a small (0.20) to moderate (0.50) Cohen’s effect size. The difference between the HHT and UC groups in the mean change was 3.9 for a small to moderate effect size. This value is close to the commonly used minimum mean change score for the DAS (3.16) (Jacobson and Truax, 1991). Then, we used these values (SDchange = 10; MCID = 3.9) to calculate the sample size with PASS15 sample size software. With 210 couples assigned in a 1:1 fashion to the two groups, we will have 80% power to detect a difference of 3.9 in the change in the DAS between the HHT and UC groups (*α* = 0.05). Nonetheless, we aim to inflate our sample size to account for the design effect of clustering (design effect = 1 + (m-1)*ICC = 1.21 = 254 couples), assuming that our average group size (m) will be 8 couples and our ICC is 0.030. We further increased our sample size target to 304 couples to account for an expected 20% loss to follow-up. As such, we aim to recruit 304 couples but will have sufficient power to detect differences in the primary outcome with 210 couples.

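### The sample-size section calls 210 couples sufficient, but its own clustering allowance requires 254 analysed couples; on its inputs, power at 210 is about 72%, not 80%

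*Protocol article*

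**What the plan says.** In the protocol article, *Sample-size calculation*, the starting figure is stated as "With 210 couples assigned in a 1:1 fashion to the two groups, we will have 80% power to detect a difference of 3.9" points in DAS change, with alpha 0.05. The inputs are stated too: "we used these values (SDchange = 10; MCID = 3.9) to calculate the sample size with PASS15 sample size software".

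The section then inflates twice. A design effect of 1 + (m − 1) × ICC = 1.21 raises the number to 254, "assuming that our average group size (m) will be 8 couples and our ICC is 0.030". An expected 20% loss to follow-up raises the target to 304.

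It closes: "we aim to recruit 304 couples but will have sufficient power to detect differences in the primary outcome with 210 couples".

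The *Healing hearts together intervention* section gives the group size separately: "Planned group size is 3–8 couples". The *Usual care* section describes no study groups in the control arm.

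**The concern.** The figure of 210 is the answer before any allowance for clustering. If the ICC of 0.030 is believed, 210 couples do not deliver the stated 80%. If it is not believed, the step to 254 has no basis. The two statements cannot both stand.

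The closing sentence also does not say whether 210 counts couples recruited or couples analysed. If recruited, the attrition allowance is lost as well.

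What is at stake is how the result is read. The trial has been running since October 2019, and the *Participants* section reports that eligibility was narrowed in July 2023. If enrolment ends short of 304, this sentence is the one that would be cited to call a null primary result adequately powered. On the plan's inputs, the type II error at 210 analysed couples is about 28% rather than 20%.

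**Working it through.** **Inputs, all from *Sample-size calculation*:** SD of change 10; difference 3.9; alpha 0.05; 1:1 allocation; m = 8 couples; ICC 0.030; loss 20%. Sidedness is not stated. A two-sided test reproduces the plan's figure, whereas a one-sided test would give about 88% at 210.

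**Method.** Two-sample comparison of means with the noncentral t. With n couples per arm and design effect DE in both arms, the standard error is SE = SD × √(2 × DE / n), and the noncentrality is 3.9 / SE.

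**1. The plan's own figures.**
- n = 105, DE = 1: SE = 10 × √(2/105) = 1.380; 3.9/1.380 = 2.826; power 80.3%. This reproduces the stated 80%, so 210 is the number for independent couples.
- DE = 1 + 7 × 0.030 = 1.21; 210 × 1.21 = 254.1. This reproduces 254.

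**2. Power with the plan's design effect.**

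| Couples | Analysed | Effective (analysed / 1.21) | SE | 3.9/SE | Power |
|---|---|---|---|---|---|
| 210 analysed | 210 | 173.6 | 1.518 | 2.569 | 72% |
| 210 recruited, 20% lost | 168 | 138.8 | 1.697 | 2.298 | 63% |
| 254 analysed | 254 | 209.9 | 1.380 | 2.825 | 80% |

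A normal approximation gives 72.9%, 63.2% and 80.7%, so the method of calculation does not matter here.

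**3. Milder clustering.** The plan uses the top of the planned group-size range as the average and applies the design effect to the ungrouped UC arm. Both choices overstate the penalty. With clustering in HHT only, SE = SD × √((1 + DE)/n).
- HHT only, DE 1.21: 76% at 210 analysed and 67% at 168. By the normal approximation, 80% power needs about 228 analysed couples.
- HHT only, m = 5.5 (the midpoint of 3 to 8, an assumption), DE = 1 + 4.5 × 0.030 = 1.135: 78% at 210 analysed.

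**4. Both partners.** The sizing takes one score per couple, while the primary model uses each individual's DAS. If partners' changes correlate at ρ, the SD of the couple mean is 10 × √((1 + ρ)/2). The article gives no ρ, so these values are assumptions, with DE 1.21 in both arms:

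| ρ | SD of couple mean | Power, 210 analysed | Power, 210 recruited (168 analysed) |
|---|---|---|---|
| 0.5 | 8.66 | 84% | 75% |
| 0.7 | 9.22 | 79% | 70% |
| 0.9 | 9.75 | 75% | 65% |

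**The case against.** The strongest reply is that the sizing calculation is not the planned analysis, and that the planned analysis is more efficient. The model uses both partners and adjusts for baseline DAS instead of testing change scores.

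- Both partners: with ρ = 0.5, power at 210 analysed is 84% with DE 1.21 in both arms, or 87% with clustering in HHT only.
- Baseline adjustment alone: the SD of change shrinks by √((1 + r)/2), where r is the baseline to follow-up correlation (equal variances assumed). For r from 0.6 to 0.9, power at 210 analysed runs from 82% down to 75% with DE in both arms, and from 85% down to 78% with HHT-only clustering.

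So 210 analysed couples may in fact give about 80%. This stands as a possibility, but it does not support the sentence. The correlations are not in the article, and the article offers neither gain as a reason for 210.

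Three further points are fair. The 72% takes the plan's own design effect at face value, and a better-specified one narrows the gap to 2 to 4 points. The 63% applies only if 210 means recruited; reading it as analysed is at least as natural, and then only the clustering allowance is dropped. Finally, the same sentence keeps 304 as the target, and no stopping rule is tied to 210. The risk therefore lies in how a shortfall would be interpreted, not in a planned early stop.

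**Conclusion.** The concern holds. The closing sentence contradicts the calculation it summarises: 210 yields the stated 80% only if the clustering allowance is ignored.

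On the plan's inputs (one score per couple, SD 10, difference 3.9, two-sided 5%, DE 1.21 in both arms), power is about 72% at 210 analysed couples, and 254 analysed are needed for 80%. If 210 are recruited and 20% are lost, power is about 63%. Restricting clustering to HHT gives 76% at 210 analysed; also assuming a mean group of 5.5 couples gives 78%. All of these are below the stated 80%.

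This does not prove that the planned two-partner, baseline-adjusted model would be under-powered at 210. It shows that the power claimed at 210 is unsupported, and wrong on the assumptions the article chose.

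**What to change.** 1. Delete the claim of sufficient power at 210 couples. If a figure for 210 is kept while the present assumptions stand, report about 72% for 210 analysed and 80% for 254 analysed.
2. Preferably, replace the calculation with one that matches the primary model: two partners per couple with a stated within-couple correlation and its source, clustering in the HHT arm only, and a mean group size that is realistic against the planned 3 to 8 (or taken from groups already run). If the gain from baseline adjustment is claimed, state the correlation assumed. A short range over the correlations would suffice.
3. Label every figure as couples recruited or couples analysed.

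The cost is a text correction and one recalculation. It needs no extra couples and no change to the 304 target, the outcome or the model. Under the present assumptions the power reported at 210 becomes less favourable; under a documented two-partner calculation it may not.

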#### Planned statistical analyses

SPSS and HLM statistical software will be used to analyze the study data. Demographic and clinical variables reported by participants who complete assessments will be compared to those lost to follow-up to verify the representativeness of the cohort. Analyses will be with the intent to treat sample. Research staff record all cases of missing data, including non-retention of participants or withdrawal of consent. Where data are missing, the frequency and reasons for missing data will be recorded. Missing data will be statistically examined for patterns of systematic missingness, and an appropriate missing data strategy will be employed. In situations where data are missing, the data collected up to that point will be used, provided the participant has not withdrawn their consent or requested that the information be removed. For the *primary outcome*, a multilevel analysis of covariance with individuals’ DAS values at 8 weeks as the dependent variable and DAS baseline scores as the covariate at level 1 of the model. The study conditions (HHT vs. UC) to which couples were assigned will be dummy-coded and entered at level 2. To evaluate *secondary outcomes,* a three-level multi-level model for repeated measurements will be utilized. The analysis will include repeated measurements within individuals in Level 1, between-individual variability in Level 2, and couples in Level 3. Within-couple slope variances will be fixed at Level 2 but allowed to vary at Level 3 (Atkins, 2005). A linear parameter will model changes in outcomes from baseline to 8 weeks to 24 weeks. The study condition (HHT vs. UC) will be dummy-coded and modeled as a fixed effect at Level 3. Baseline patient control variables will be entered at Level 2. Binary outcomes will be modeled utilizing a logit link. Improved model fit between nested models will be evaluated using deviance statistics and a chi-square distribution. Effect sizes will be assessed with the pseudo-R squared statistic or Cohen’s d when appropriate. Full maximum likelihood estimation method will be applied for all analyses. For both primary and secondary analyses, we will also conduct stratified analyses for all outcomes by sex (male/female), CR participation (yes/no), and relationship quality (distressed/not distressed on the DAS).

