## Method

### Design

The study is a single-centre, RCT with parallel group design. After a baseline assessment, participants are randomized in a 1:1 fashion, using a computer-generated sequence utilizing permuted blocks of 4, 8 and 10 initiated by the institutional methods centre, to the HHT program or to UC. Since sex and participation in CR can have an impact on the study outcomes, randomization is stratified by patient sex (male/female) and participation in the University of Ottawa Heart Institute (UOHI) CR program (yes/no). The trial began in October 2019 and data collection is ongoing. The protocol was approved by our institutional research ethics board (OHSN-REB# 20190101-01H) and all participants provide informed consent. Figure 1 depicts the study design and cohort flow.

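### The primary ANCOVA leaves out the two randomisation strata, patient sex and CR participation; if they predict 8-week DAS, the reported standard error is somewhat too large and the test conservative

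*Protocol article*

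**What the plan says.** The Design section of the protocol article gives both the stratification and its reason: "Since sex and participation in CR can have an impact on the study outcomes, randomization is stratified by patient sex (male/female"). The second factor, CR, is given there as a yes/no variable for the hospital's own programme. Allocation is 1:1 within strata, "using a computer-generated sequence utilizing permuted blocks of 4, 8 and 10".

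Planned statistical analyses sets out the primary model term by term. It has "DAS values at 8 weeks as the dependent variable and DAS baseline scores as the covariate at level 1 of the model", and then: "The study conditions (HHT vs. UC) to which couples were assigned will be dummy-coded and entered at level 2". No other term is listed.

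The same section mentions two further things that bear on this point:

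- In the description of the three-level repeated-measures model for secondary outcomes: "Baseline patient control variables will be entered at Level 2". These variables are not identified, and the sentence is not attached to the primary model.
- As an addition to the primary and secondary analyses: "we will also conduct stratified analyses for all outcomes by sex (male/female), CR participation (yes/no").

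**The concern.** Randomisation and analysis do not match. Permuted blocks within the four sex-by-CR strata keep the arms nearly balanced on both factors, so differences between strata largely drop out of the treatment contrast. The estimate is then less variable than under simple randomisation. A model that does not contain the strata cannot see this. It counts between-stratum variation as residual noise and reports a standard error that is too large whenever the factors predict the outcome beyond baseline DAS.

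At stake is the width of the confidence interval for the primary effect, a test that runs below its nominal 5%, and some power in a trial planned at 80%. The planned analyses within sex and CR groups do not repair this. They give separate estimates by subgroup and leave the pooled primary estimate and its standard error as they were.

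**Working it through.** **Inputs.** From Sample-size calculation: "SDchange = 10; MCID = 3.9", alpha 0.05, 80% power, 210 couples allocated 1:1. From Design: stratified blocks of 4, 8 and 10. Not in the documents, and therefore assumed: R², the share of the residual variance behind the treatment contrast that patient sex and CR explain after baseline DAS. It is shown at 0, 2%, 5%, 10% and 20%.

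**Step 1: the plan's own figure.** Couples per arm = 2 × (1.960 + 0.842)² × 10² / 3.9² = 103.2, rounded up to 104, so 208 in total against 210 stated. At 105 per arm, power is 80.7% by the normal approximation and 80.3% by the noncentral t. A one-sided test would need 164 in total, so the plan's figure is two-sided.

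**Step 2: the two standard errors.** With 105 couples per arm:

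- reported without the strata: 10 × √(2/105) = 1.380
- true, under stratified allocation: 10 × √(1 − R²) × √(2/105)
- ratio of reported to true: 1/√(1 − R²)

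**Step 3: alpha and power.**

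- actual alpha without the strata = 2 × [1 − Φ(1.96/√(1 − R²))]
- power without the strata = Φ[(3.9 − 1.96 × reported SE)/true SE]
- power with the strata = Φ[3.9/true SE − 1.96]

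For R² = 10%, the true SE is 1.380 × √0.90 = 1.309. Power without the strata is Φ[(3.9 − 2.705)/1.309] = Φ(0.913) = 81.9%. Power with them is Φ(2.979 − 1.96) = Φ(1.019) = 84.6%.

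| Assumed R² | Reported/true SE | Actual alpha | Power without strata | Power with strata | Gain (points) |
|---|---|---|---|---|---|
| 0 | 1.000 | 5.0% | 80.7% | 80.7% | 0 |
| 2% | 1.010 | 4.8% | 80.9% | 81.4% | 0.5 |
| 5% | 1.026 | 4.4% | 81.3% | 82.6% | 1.3 |
| 10% | 1.054 | 3.9% | 81.9% | 84.6% | 2.7 |
| 20% | 1.118 | 2.8% | 83.3% | 88.5% | 5.2 |

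The SE ratio and alpha columns do not depend on the SD of 10. The power columns do: they use the plan's SD of change as the residual SD and take the couple as the unit, as the plan's 210 does.

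**Step 4: check by simulation.** Stratified blocks of 4, 8 and 10 were simulated with 210 couples and 4,000 runs per setting, assuming 25% of couples in one sex stratum and 60% in CR. At R² = 10% with no treatment effect:

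- without the strata: mean reported SE 1.384, empirical SE 1.319, rejection rate 4.1%
- with the strata: mean reported SE 1.312, empirical SE 1.319, rejection rate 5.3%

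The empirical SE is the same in both rows. Stratification has already delivered the precision; the model without the strata does not report it. At R² = 20%, simulated power was 82.6% without and 87.6% with the strata.

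**The case against.** **The documents do not show that these factors predict DAS.** The Design section speaks conditionally and of the outcomes in general, which also include cortisol, lipids, blood pressure and physical activity. Baseline DAS may absorb most of what sex and CR could explain. This stands: the size rests on an assumed R², and at zero there is no effect.

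**An article condenses, and the full analysis plan may add the strata.** This stands in part. The sentence does not say that no other covariate will be used. But the primary model is written out term by term, and control variables are mentioned only for the secondary model, so a reader following the text would fit the primary model without the strata.

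**Stronger readings that a reader might draw, and that are not supported:**

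- *That the primary result would be biased or give too many false positives.* The error runs the other way: alpha falls below 5% and the interval is too wide.
- *That the power gain is the gap between adjusted power and the planned 80.3%.* If the strata matter, the unadjusted model also has more than its planned power, because the estimate is already less variable. The comparison must be made within the same scenario, as in the table.
- *That the secondary models omit the strata as well.* Those models have baseline patient control variables that the article does not name; sex and CR may be among them.
- *That the lack of a patient/partner term distorts the treatment test.* Couples are randomised and each complete couple contributes one of each role, so role is balanced across arms. In a simulation of 210 couples with an assumed 5-point role difference, the mean treatment SE was 1.168 with and without the term.

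**Conclusion.** The point holds in a limited form. The trial stratifies on two factors that it considers potentially prognostic, and the primary model as written contains neither. If they explain residual 8-week DAS variance, the reported SE is too large and the test conservative. Across an assumed R² of 2% to 10%, the interval is about 1.0% to 5.4% too wide, alpha is about 4.8% to 3.9%, and 0.5 to 2.7 points of power are given away at 210 couples. The direction is certain if the factors matter; the size is modest and cannot be fixed from the documents. It does not threaten the validity of a positive result. It is worth correcting because the improvement is essentially free, and because adding covariates after the results are known would look data-driven.

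**What to change.** Add patient sex and CR participation to the primary multilevel ANCOVA as couple-level (level 2) fixed effects, next to condition, and say so before the data are analysed. Use the values recorded at randomisation. Follow-up assessments collects CR enrolment again at 8 weeks and 6 months; that is a post-randomisation variable and must not stand in for the stratum. Keep the analyses by sex and CR as supplementary.

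The cost is a change of wording and two degrees of freedom. Both variables are already held for every randomised couple, and neither the sample size nor the conduct of the trial changes.

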**Objectives:**

The primary objective is to examine the difference in relationship quality between the 8-week HHT intervention group and usual care (UC) at program completion. Secondary objectives include evaluating the impact of HHT on relationship quality at 6 months, and mental health, quality of life, and cardiovascular risk factors measured at 8 weeks and 6 months post-intervention, as compared to usual care.

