## Study aims and objectives

The primary aim of this RCT is to examine the efficacy of the 8-week HHT program on the relationship quality of patients with CVD and their romantic partners at 8 weeks, in comparison to UC. We expect that those assigned to the HHT condition will have greater improvements in RQ scores (as measured by the dyadic adjustment scale) than will those in UC. Secondary aims include measuring the impact of the program on relationship quality at 6 months and secondary outcomes, including cardiovascular and cortisol reactivity, inflammatory markers, mental health, quality of life, health behaviors, and cardiovascular risk factors, at 8 weeks and 6 months. We expect greater improvements in all secondary outcomes among HHT participants than in UC participants. This paper describes the study design, objectives and method.

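### One straight line over weeks 0, 8 and 24 cannot give the separate 8-week and 6-month effects that the secondary objectives ask for

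*Protocol article*

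**What the plan says.** Two parts of the protocol article set the question. The abstract's objectives state: "Secondary objectives include evaluating the impact of HHT on relationship quality at 6 months". The section on study aims repeats this and adds cortisol reactivity, inflammation, mental health, quality of life and health behaviours, ending the list with "cardiovascular risk factors, at 8 weeks and 6 months". The secondary estimands are therefore differences between HHT and usual care at two named visits. Table 1 labels the 6-month visit as week 24.

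The section on planned statistical analyses sets the model. For secondary outcomes "a three-level multi-level model for repeated measurements will be utilized". On time, it states: "A linear parameter will model changes in outcomes from baseline to 8 weeks to 24 weeks". On treatment, it states: "The study condition (HHT vs. UC) will be dummy-coded and modeled as a fixed effect at Level 3". It does not say whether condition acts on the intercept, the slope or both, how time is coded, or whether the arms share a baseline mean. It plans deviance tests between nested models but names no curved, piecewise or categorical time term.

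The intervention section gives the treatment period: "Couples are invited to attend 8 weekly 2-h sessions". About 16 of the 24 weeks therefore fall after the last session.

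The primary outcome, DAS at 8 weeks, has its own baseline-adjusted multilevel ANCOVA and does not use the linear time term.

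**The concern.** The objectives need two treatment effects per outcome, and the stated model has one linear time parameter. A straight line assumes that the treatment difference builds up at the same rate during the sessions and in the 16 weeks after them. Nothing in the article supports that. A gain that is kept, or one that partly fades, is at least as plausible and bends at week 8.

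At stake is what the trial can say about its secondary outcomes: whether there was a benefit when the programme ended, and whether it lasted. Durability of relationship quality at 6 months is the first secondary objective named. A single slope merges the two questions into one number, and the 8-week answer suffers most.

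**Working it through.** **Inputs.** Visits at 0, 8 and 24 weeks (Table 1). A difference of 3.9 DAS points and an SD of change of 10 (sample-size section). The course after week 8 is not given, so it is assumed and shown as a range. The 3.9 only sets a scale, and every effect below is proportional to it.

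**The plan's own figure.** n per arm = 2(1.960 + 0.842)² × 10² / 3.9² = 2 × 7.849 × 100 / 15.21 = 103.2, or 104. The t-test version needs 104.2, so 105 per arm and 210 couples, as stated. That figure serves the primary outcome; none is given for the secondary model.

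**Condition acting on the slope.** With slope difference b, the effect on change from baseline at time t is b·t. The ratio of week 24 to week 8 is 24/8 = 3 in weeks, or 2/1 = 2 with visits coded 0, 1, 2, whatever the data show.

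**Arm-specific intercepts, time in weeks.** With complete balanced data, the fitted slope difference is the least-squares slope through the three arm differences. Mean time is 32/3 = 10.67; centred times are −10.67, −2.67 and 13.33; their sum of squares is 298.67. For true differences 0, 3.9, 3.9:
- slope = 3.9 × (−2.67 + 13.33) / 298.67 = 0.139 per week
- intercept = 2.6 − 0.139 × 10.67 = 1.11
- slope-implied effects: 8 × 0.139 = 1.11 and 24 × 0.139 = 3.34
- fitted arm differences: 1.11, 2.23 and 4.46, the first being a false gap at baseline

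**Common baseline, time in weeks.** b = t′V⁻¹y / t′V⁻¹t, where y is the vector of arm differences and V is compound symmetric with correlation ρ. V⁻¹ is proportional to I − cJ, with J the matrix of ones and c = ρ/(1 + 2ρ). At ρ = 0.5, c = 0.25. For 0, 3.9, 3.9: b = (124.8 − 0.25 × 32 × 7.8) / (640 − 0.25 × 32²) = 62.4 / 384 = 0.1625, giving 1.30 and 3.90. At ρ = 0.7 the result is 1.22 and 3.66; at ρ = 0 it is 1.56 and 4.68.

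**Visits coded 0, 1, 2, arm-specific intercepts.** The slope is half the week-24 difference, and the week-8 data drop out of it.

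| True effect, weeks 8 and 24 | Slope-implied, weeks | Fitted differences at 0, 8, 24 | Common baseline, ρ = 0.5 | Slope-implied, 0/1/2 |
|---|---|---|---|---|
| 3.9, 3.9 (kept) | 1.11, 3.34 | 1.11, 2.23, 4.46 | 1.30, 3.90 | 1.95, 3.90 |
| 3.9, 1.95 (half lost) | 0.42, 1.25 | 1.39, 1.81, 2.65 | 0.65, 1.95 | 0.975, 1.95 |
| 3.9, 0 (fully lost) | −0.28, −0.84 | 1.67, 1.39, 0.84 | 0, 0 | 0, 0 |
| 1.3, 3.9 (proportional to weeks) | 1.30, 3.90 | 0, 1.30, 3.90 | 1.30, 3.90 | 1.95, 3.90 |

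In the first three rows, week 8 is understated in every column. Week 24 can be low, exact or high.

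**Condition as a main effect only.** The model gives the mean of the three differences, with baseline included: 2.6, 1.95 or 1.3 for the first three rows. No visit-specific effect exists.

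**Power, as illustration.** Take 105 per arm, compound symmetry, no random-slope variance and no clustering. The slope test in weeks has standard error √(100 / (298.67 × 105)) = 0.0565. Power is 69% if the effect is kept, 15% if half lost and 10% if fully lost, the last mostly in the wrong direction. A direct 8-week contrast of 3.9 has 80.7%. With 0/1/2 coding the slope test has 81%, 29% and 5%, so the loss for a kept effect also depends on coding.

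**The case against.** The strongest objection is that the size of the error rests on matters the article leaves open. Time coding, the baseline constraint and the within-person correlation are details that a condensed article may leave to the full plan, and no course after week 8 is given. This stands, and it limits the claim in four ways.

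- A reader might infer that both visit effects are misstated. The article does not support that. With 0/1/2 coding, or a common baseline at correlation 0.5, the week-24 value is exact for a kept, half-lost or fully lost effect, and only week 8 is wrong.
- A reader might infer that a kept effect is overstated at 24 weeks. The fitted difference of 4.46 is too high, but the slope-implied 3.34 from the same fit is too low. The direction depends on which quantity is read.
- A reader might infer that a fully lost effect would appear as harm. The slope is negative in weeks with arm-specific intercepts, but zero under the other two specifications in the table.
- The arithmetic does not carry over directly to binary outcomes under a logit link, and with dropout (20% is expected) the least-squares results are approximate.

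A second objection is that the planned deviance tests could reveal curvature. No non-linear alternative is named, and choosing the time shape from the fit would make the secondary estimand depend on the data.

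A third is that the effect may grow steadily as couples practise what they learned. If it grew in proportion to the time variable, the line would fit without error. The article neither predicts nor excludes this, and a model that needs it to be true is a poor default when sessions stop at week 8.

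The structural point survives all three: the linear form is stated, not omitted, and no choice of coding lets one slope return two free visit effects. With arm-specific intercepts the fitted differences are not tied at 3 to 1, but they must still lie on a line with a baseline gap that randomisation says should be zero on average.

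**Conclusion.** The linear time model does not match the secondary objectives. It cannot estimate the 8-week and 6-month effects separately under any reading of how condition enters.

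If the effect is kept or fades after week 8, the 8-week effect is understated. For a true 3.9 that is kept, with time in weeks, the slope implies 1.1 (arm-specific intercepts, with a fitted difference of 2.2) or 1.3 (common baseline, correlation 0.5). These figures assume complete data, a continuous outcome and no true baseline difference. A delayed effect would err the other way at week 8. Nothing firm can be said about the size or sign of an error at week 24.

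A reader might take this as a threat to the trial's main result. It is not: the primary 8-week DAS ANCOVA is a separate model. The point covers the secondary outcomes, including DAS at 6 months.

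**What to change.** For secondary outcomes, replace the linear term with visit as a categorical factor (baseline, week 8, week 24) and add condition-by-visit terms. Either constrain the baseline means to be equal across arms or use baseline as a covariate. Replace the random linear slope with a visit-level covariance within person and within couple. Report the HHT minus usual care contrast at week 8 and at week 24 separately; for binary outcomes use the same terms on the logit scale. A piecewise slope with a knot at week 8 is equivalent for the means, because three visits are then fitted by three parameters per arm.

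In the illustration this recovers the assumed effect at each visit under every profile. It needs no new data. The cost is a change of wording and about one extra fixed-effect parameter per outcome: five with equal baselines, against four for an intercept and slope in each arm. Power is slightly lower if the effect truly grows linearly to week 24. The article describes data collection as ongoing, so the change should be fixed and dated before any comparison by arm.
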